#### 2.11.2. General Analysis

We will conduct all analyses according to the intention-to-treat principle, where we analyse data as randomised regardless of adherence to the research protocol. An additional per-protocol analysis will be performed for exploratory reasons if the drop-out rate exceeds 5% of the total trial population. We will assess whether the statistical and clinical significance thresholds apply [30], based on the estimated intervention effects and power estimations used in the sample size.

We will base our main conclusions on the primary outcome, following the intention-to-treat principle, assuming a type 1 error threshold of 5% (*p* < 0.05), with the relative risk and confidence intervals (CIs) calculated at the 95% level and a type 2 error threshold of 0.2 (80% statistical power).

Regression analyses will be adjusted for the factors used in the randomisation (the exclusive presence of the family health strategy model in the practice and the social development index stratum), assessing for significant interactions between them and the outcome variables. We will consider the results of secondary or exploratory outcomes as hypothesis-generating only. No subgroup analysis besides the one using the stratification factors is planned; if executed, these results will also be hypothesis-generating only.

Categorical variables will be described as absolute and relative frequencies, and continuous variables as medians (interquartile range) or means (standard deviation) according to the distribution of the variable. Missing data will be handled according to Jakobsen’s recommendations [31]; briefly, we will include participants in the primary analysis of all outcomes and anticipate a less than 5% missing value rate. We will then perform a secondary analysis considering the use of multiple imputations and present best-worst and worst-best case scenarios if it is not valid to ignore missing data.

To account for clustering within each primary care practice, all outcomes will be analysed using generalised estimating equation methods (GEE) [32]. All analyses will additionally be adjusted for the stratification variables used in the randomisation. The software R (R Foundation for Statistical Computing, Vienna, Austria; version x64 3.6.0, including the package “geepack” for GEE) [33] and STATA will be used for statistical analysis.

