## 3. Results

### 3.1. Data Collection Methods

We will collect primary care practices’ data to assess stratification factors (presence of family health strategy exclusively in the practice and population’s socioeconomic status) from Rio’s publicly accessible health system websites [16,34,35,36]. We will obtain a monthly report from the Health Secretariat about hospital admissions containing name, birth date, social identification number (CPF), national health system identification number (CNS), address, hospital, admission date, admission diagnosis, outcome (discharge/transference/death), discharge diagnosis, discharge date, and procedures. Data about the patient’s primary care practice (name, address, phone number, responsible physician) will be collected from the public website *Onde Ser Atendido* [23].

The recruiters will collect baseline data about the physicians through direct inquiry during recruitment. For patient data, we will receive a report extracted from primary care electronic health records including patients’ clinical data, completed during patient recruitment through direct inquiry, to minimise missing data. We will insert data using a REDCap © platform digital form. Baseline collected variables and a description of form fields are summarised in Table 2.

In the intervention group, during teleconsultation, the primary care physician and the teleconsultant (cardiologist) will insert data about the process using a specific form on a digital e-consultation platform designed for the project. The form contains the same fields as the REDCap© form, the reason for teleconsultation, and boxes for text messages. Data from the e-consultation platform will be exported to REDCap© for storage and analysis. In the control group, the recruiter will inform the physician that data from patients with heart failure who were recently discharged from the practice will be collected at baseline and after six months of allocation. We will train all the physicians in using the e-consultation platform.

During recruitment, interviewers assigned to the project will apply paper questionnaires about quality of life (EQ-5D-5L questionnaire) [37,38,39] and heart failure symptoms frequency (Symptom Status Questionnaire—SSQ-HF) [40,41] for baseline assessment.

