After six months of the allocation, we will repeat the described data collection for admissions, serious adverse events, and primary care electronic health records and re-apply EQ-5D-5L and SSQ-HF questionnaires. We will collect mortality data from a report on mortality provided by the Health Secretariat.

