### 3.2. Outcomes

The primary outcome will be a composite of all-cause mortality or one or more hospital readmissions. Any pre-hospital or hospital stay because of heart failure will be considered as a readmission [42,43]. Secondary outcomes will include hospital-free days within 180 days [44,45,46], serious adverse events (defined as any adverse event that results in death, is life-threatening, requires hospitalisation or prolongation of existing hospitalisation, or results in persistent or significant disability or incapacity, measured in municipality admission reports), frequency and intensity of heart failure signs and symptoms, measured using the Symptom Status Questionnaire—Heart Failure—Brazilian Version (Appendix A) [40,41], computed as a 0 to 84 score, and health-related quality of life, measured using the EQ-5D-5L questionnaire [37,38] scored using a value set validated for the Portuguese version [39] on a visual-analogic scale (0 to 100).

An exploratory outcome will be physicians’ adherence to guidelines, comparing prescription data to guidelines and quality standards using a compliance score (Table A1 in Appendix B) [47,48,49,50]. We will measure all outcomes at the patient level, at baseline when meaningful, and after six months of allocation.

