## Figures and Tables

**Figure 1 ijerph-20-05933-f001:**
[figure not shown]
Study workflow.

**Table 1 ijerph-20-05933-t001:** Participant Timeline.

Enrolment	T_−1_	T_0_	T_6_ (Close-Out)
General practice stratification and randomisation	X		
Patient eligibility screening using municipality data	X		
Invitation to participate (patient)	X		
Invitation to participate (physician)	X		
Informed consent (patient and physician)	X		
Patient allocation according to practice randomisation		X	
Intervention			
Intervention group		Teleconsultation support for the practice’s physicians (first contact and on demand)	
Control group		Usual care with follow-up of outcomes	
Assessments		T_0_	T_6_ (close-out)
1—Readmissions and Mortality (reports)			X
2—Days Alive Out of Hospital (DAOH)			X
3—Frequency of Serious Adverse Events			X
4—Symptoms Frequency and Severity		X	X
5—Quality of Life		X	X
6—Adherence to Prescribing Guidelines		X	X

**Table 2 ijerph-20-05933-t002:** Baseline Variables.

N	Variable	Field Type	Choices, Calculations, or Labels
Physician Variables—direct inquiry			
1	Name	Text	-
2	Social Identification Number (CPF)	Text	-
2	Completed years since graduation	Number	-
3	Specialisation	Option	Any/Family Medicine/Other
4	Completed years in primary care	Number	-
5	Completed years in the current practice	Number	-
6	Enrolled in a residency program	Options	No/Preceptor/1st year Resident/2nd year Resident/3rd year Resident/Program
Patient Variables—primary care electronic health record report			
1	Name	Text	-
2	Social identification number (CPF)	Text	-
3	National Health System identification number (CNS)	Text	-
4	Primary care practice	Text	
5	Gender	Options	Feminine/Masculine/Nonbinary
6	Race	Options	White/Black/Brown/Other
7	Birth date	Date	-
8	Weight (Kg)	Number	-
9	Height (cm)	Number	-
10	NYHA status	Options	1 to 4
11	Systolic blood pressure	Number	-
12	Diastolic blood pressure	Number	-
13	Heart rate	Number	-
14	Dyspnoea	Option	Yes/No
15	Leg Swelling	Option	Yes/No
16	Dizziness	Option	Yes/No
17	Fatigue	Option	Yes/No
18	Orthopnoea or paroxysmal nocturnal dyspnoea	Option	Yes/No
19	Syncope	Option	Yes/No
20	Typical chest pain	Option	Yes/No
21	Jugular vein distension	Option	Yes/No
22	Pulmonary rales	Option	Yes/No
23	ACE-I (names)	Option	ACE-I names
24	ACE-I dose	Number	-
25	ARB (names)	Option	ARB names
26	ARB dose	Number	-
27	Beta-blockers (names)	Option	BB Names
28	Beta-blockers dose	Number	-
29	Spironolactone	Option	Yes/No
30	Spironolactone dose	Number	-

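### The stated model for all outcomes gives no role to the baseline symptom, quality-of-life and adherence scores that the trial collects, which forgoes precision on these secondary and exploratory outcomes

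*Protocol article*

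**What the plan says.** Section 2.11.2 (General Analysis) states the covariates twice. First: "Regression analyses will be adjusted for the factors used in the randomisation", which it identifies as exclusive use of the family health strategy model and the Social Development Index stratum. Then, after saying that GEE is used to account for clustering within practices: "All analyses will additionally be adjusted for the stratification variables used in the randomisation". No other covariate, change score or repeated-measures model is named in the article.

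The baseline data are planned. Section 3.2 says: "We will measure all outcomes at the patient level, at baseline when meaningful, and after six months of allocation". Section 3.1 has interviewers administer EQ-5D-5L and SSQ-HF during recruitment, and after six months the team will "re-apply EQ-5D-5L and SSQ-HF questionnaires". Table 1 marks T0 and T6 for symptoms, for quality of life and for the row "6—Adherence to Prescribing Guidelines". The readmission and mortality, days-alive-out-of-hospital and serious-adverse-event rows are marked at T6 alone.

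Symptoms and quality of life are secondary in Section 3.2 and the adherence score is exploratory. Section 2.11.2 treats all such results as hypothesis-generating.

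**The concern.** For a score measured before and after, the patient's own baseline value is usually the strongest available predictor of the later value. The article collects it for three outcomes, at the cost of interviews and record extraction, and then sets out a model that contains only practice-level factors. The GEE does not fill the gap, because its stated purpose is clustering by practice and not repeated measurement of a patient.

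Two things are at stake for these outcomes. The confidence intervals are wider than the collected data require. And whatever baseline difference arises by chance between the arms stays in the estimate. In addition, if the baseline value has no stated role, a later choice between raw score, change score and baseline adjustment is harder to defend as pre-specified.

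**Working it through.** **Inputs from the article.** 80 practices of 10 patients, 800 in all (Abstract); 1:1 allocation (2.1); ICC 0.05, 5% type I error, 80% power, a 40.1% event rate and a 30% effect (2.11.1).

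**Assumptions.** Two-sided test; the ICC of 0.05 also holds for the scores and their baseline values; all 800 patients contribute; r, which the article does not give, is 0.3, 0.5 or 0.6.

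**Step 1: the plan's own figure.** The article gives no precision figure for these scores, so I reproduced its cluster number to confirm the design effect. Reading 30% as relative, 0.401 × 0.70 = 0.2807. The two-proportion formula without continuity correction gives 243 per arm. The design effect is 1 + (10 − 1) × 0.05 = 1.45, and 243 × 1.45 = 352.35, which is 36 practices per arm or 72 in total, as stated. (The 15% difference also mentioned in 2.11.1 does not lead to 72. That is a separate matter and is not used here.)

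**Step 2: without the baseline value.** Effective patients per arm: 400 / 1.45 = 275.9. Standard error of the difference: √(2 / 275.9) = 0.0851 SD. Detectable difference: (1.960 + 0.842) × 0.0851 ≈ 0.239 SD.

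**Step 3: with the baseline value, same r within and between practices.** The variance is multiplied by 1 − r², the detectable difference by √(1 − r²), and the equivalent unadjusted trial has 800 / (1 − r²) patients.

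**Step 4: with the baseline value, explaining only within-practice variation.** The variance of a mean of 10 patients is 0.05 + 0.95 / 10 = 0.145, of which 0.095 / 0.145 = 0.655 lies within practices. The variance falls by 0.655 × r².

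| Assumed r | Variance cut, same r | Detectable difference | Equivalent unadjusted N | Variance cut, within only | Detectable difference |
|---|---|---|---|---|---|
| 0.3 | 9% | 0.228 SD | 879 (+10%) | 6% | 0.231 SD |
| 0.5 | 25% | 0.207 SD | 1,067 (+33%) | 16% | 0.218 SD |
| 0.6 | 36% | 0.191 SD | 1,250 (+56%) | 24% | 0.209 SD |

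Under the same-r assumption, power at 0.239 SD rises from 80% to 83.6%, 89.9% and 93.8%.

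**Step 5: chance imbalance.** The difference between arms in the baseline score has the same standard error as in Step 2, about 0.085 SD. Under individual randomisation it would be √(2 / 400) = 0.071 SD. An imbalance of one such SD moves the unadjusted estimate by r × 0.085, which is 0.026, 0.043 or 0.051 SD for r of 0.3, 0.5 or 0.6, against a detectable difference of 0.239 SD.

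**The case against.** The strongest reply is that the article states nothing false. Adjusting for the stratification factors is right. The word "additionally" can be read as setting a minimum, and a sentence covering every outcome need not list a covariate that exists for only three of them. An analysis plan that is not shown could add it. This stands to a degree: a reader might infer that baseline adjustment is excluded, but the text does not say so. What remains is that the article goes beyond silence. It says that "all outcomes will be analysed using generalised estimating equation methods (GEE"), twice gives the adjustment set for those analyses, and assigns the T0 scores no analytic use.

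A reader might also infer that the unadjusted estimates are biased. The documents do not support that. Under sound randomisation the estimate is unbiased on average, and the realised imbalance is random error that the confidence interval already covers. Nor do the documents show that recruitment would make the arms differ systematically. Table 1 and Sections 2.7.1 and 2.7.3 are not clear on the order of randomisation and recruitment, but that is a separate question and does not establish an imbalance.

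Finally, the gain rests on an assumed r. Baseline is taken soon after a heart failure discharge, nothing in the article indicates how strongly it predicts the six-month score, and at r = 0.3 the gain is small. This limits the size of the point but not its direction.

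**Conclusion.** The point holds as a forgone precision gain on SSQ-HF, EQ-5D-5L and the adherence score. It is not an error that threatens the trial. The variance reduction given up runs from about 6% (r = 0.3, baseline explaining only within-practice variation) to about 36% (r = 0.6, same correlation at both levels). Both ends rest on assumed correlations and on carrying the ICC of 0.05 over to these scores.

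A reader might take this further and doubt the main conclusion or the sample size. Neither is touched: Section 2.11.2 bases the main conclusions on the binary composite, which has no baseline value, and the 72 and 80 clusters were set for that outcome. Because the affected outcomes are secondary or exploratory, the change is worth making for its low cost and not for any urgency.

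**What to change.** Add to Section 2.11.2: the six-month SSQ-HF, EQ-5D-5L and treatment adherence scores are each analysed by GEE, with the patient's baseline value of the same measure as a covariate alongside the two stratification factors. State in the same place how missing baseline values are handled, by a rule that does not use the allocated arm, and set it next to the existing missing-data text (multiple imputation and best-worst/worst-best scenarios) so that the two do not conflict.

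The cost is one or two sentences. No new data, visits or patients are needed, and the analysis of the primary outcome stays as it is.

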## Abstract

Heart failure is a prevalent condition and a frequent cause of hospital readmissions and poor quality of life. Teleconsultation support from cardiologists to primary care physicians managing patients with heart failure may improve care, but the effect on patient-relevant outcomes is unclear. We aim to evaluate whether collaboration through a novel teleconsultation platform in the Brazilian Heart Insufficiency with Telemedicine (BRAHIT) project, tested on a previous feasibility study, can improve patient-relevant outcomes. We will conduct a parallel-group, two-arm, cluster-randomised superiority trial with a 1:1 allocation ratio, with primary care practices from Rio de Janeiro as clusters. Physicians from the intervention group practices will receive teleconsultation support from a cardiologist to assist patients discharged from hospitals after admission for heart failure. In contrast, physicians from the control group practices will perform usual care. We will include 10 patients per each of the 80 enrolled practices (n = 800). The primary outcome will be a composite of mortality and hospital admissions after six months. Secondary outcomes will be adverse events, symptoms frequency, quality of life, and primary care physicians’ compliance with treatment guidelines. We hypothesise that teleconsulting support will improve patient outcomes.

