### 2.7. Assignment of Interventions

#### 2.7.1. Allocation—Sequence Generation

Primary care practices from Rio will be stratified into four strata according to two factors, each having two levels: the family health strategy model running exclusively in the practice (presence or absence) and the Social Development Index (≤0.60 or >0.60). [24]. The research team has concluded that both factors are important determinants of the work process quality and patient outcomes, respectively [5,25,26].

We will randomise practices within each stratum after recruitment to control or intervention groups, using a computerised random number generator on a simple 1:1 allocation ratio to increase homogeneity between the groups. Once we randomise the practices, we will allocate the patients and apply the intervention of the physician or follow-up, depending on the group.

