31	Furosemide	Option	Yes/No
32	Furosemide dose	Number	-
33	Digoxin	Option	Yes/No
34	Digoxin dose	Number	-
35	Syncope	Option	Yes/No
36	Hypertension	Option	Yes/No
37	Diabetes	Option	Yes/No
38	Dyslipidaemia	Option	Yes/No
39	Coronary artery disease	Option	Yes/No
40	Peripheric artery disease	Option	Yes/No
41	Cerebrovascular disease	Option	Yes/No
42	Atrial fibrillation	Option	Yes/No
43	Chagas disease	Option	Yes/No
44	Pulmonary chronic obstructive disease	Option	Yes/No
45	Creatinine	Number	-
46	Echocardiogram ejection fraction	Number	-

ACE-I—angiotensin conversion enzyme inhibitors; ARB—angiotensin receptor blockers; BMI—body mass index; NYHA—New York Heart Association.

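### The only adjustment named for the primary model is for two practice-level factors; prespecifying a few patient covariates already collected would add modest precision

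*Protocol article*

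**What the plan says.** The primary outcome is binary. Section 3.2: "The primary outcome will be a composite of all-cause mortality or one or more hospital readmissions". The Abstract sets the time point: "The primary outcome will be a composite of mortality and hospital admissions after six months". Section 2.11.2 analyses every outcome by GEE with practices as clusters, and reports the primary result "with the relative risk and confidence intervals (CIs) calculated at the 95% level".

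Section 2.11.2 mentions adjustment twice. It first names the two randomisation factors, then repeats: "All analyses will additionally be adjusted for the stratification variables used in the randomisation". Section 2.7.1 shows that both belong to the practice: "Primary care practices from Rio will be stratified into four strata according to two factors, each having two levels". They are exclusive use of the family health strategy and the Social Development Index, cut at 0.60. The Discussion names stratification and randomisation as the trial's protection against bias and does not mention patient-level adjustment.

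Patient data are nevertheless gathered at baseline. Section 3.1 takes them from the primary care record, "completed during patient recruitment through direct inquiry, to minimise missing data". Table 2 lists birth date, gender, NYHA class, blood pressure, creatinine, comorbidities and "Echocardiogram ejection fraction". The municipal report adds admission and discharge dates, from which the index length of stay follows.

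**The concern.** A patient's own severity can be expected to predict death or heart failure readmission. Two binary practice-level factors capture little of the variation between patients in one practice. A model that leaves out measured predictors of a binary outcome is usually somewhat less precise than one that includes them, and here the data are collected anyway. At stake is the width of the confidence interval for the result on which the main conclusion rests.

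There is a second, conditional point. If patients enter or leave the study differently by arm, practice-level adjustment does nothing about the resulting difference in severity. Adjustment for patient covariates would remove the measured part.

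**Working it through.** **1. The plan's own figure.** Inputs from Section 2.11.1: control risk 40.1%, effect 30%, ICC 0.05, 10 patients per cluster, 5% type I error, 80% power. Read as a relative reduction, p1 = 0.401 and p2 = 0.401 × 0.70 = 0.2807, with mean 0.34085. Sidedness is not stated; two-sided reproduces the figure.

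- n per arm = [1.96√(2 × 0.34085 × 0.65915) + 0.8416√(0.401 × 0.599 + 0.2807 × 0.7193)]² / 0.1203² = (1.3138 + 0.5596)² / 0.01447 = 242.5, so 243.
- Design effect = 1 + 9 × 0.05 = 1.45.
- 243 × 1.45 = 352.35 per arm (705 in total), so 36 clusters per arm and 72 in all, as stated.
- Power is 80.9% at 72 clusters and 84.8% at the planned 80.

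No patient covariate enters this calculation.

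**2. Gain by formula.** Suppose covariates explain a share R² of outcome variance. The effective number per arm is then 400 / [1.45 × (1 − R²)] at 80 clusters, or 360 in place of 400 at 72. R² is assumed.

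| R² | Total needed | Power, 72 clusters | Power, 80 clusters |
|---|---|---|---|
| 0 | 705 | 80.9% | 84.8% |
| 5% | 669 | 82.9% | 86.6% |
| 10% | 634 | 84.8% | 88.3% |
| 15% | 599 | 86.8% | 90.0% |
| 20% | 564 | 88.7% | 91.7% |

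**3. Gain by simulation.** Setting: 80 practices of 10, control risk 40.1%, relative risk 0.70, log-link GEE with exchangeable correlation and robust standard errors, with and without one patient-level risk score. The strength of the score is assumed.

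- Mean estimated variance of log RR, adjusted over unadjusted (400 trials per scenario, latent-scale ICC 0.05): 0.950, 0.899 and 0.861 for C-statistics 0.63, 0.70 and 0.73. The equivalent in extra patients is 800 × (1/ratio − 1), about 42, 90 and 129. The empirical ratios from the same trials were 0.97, 0.89 and 0.92, which are noisy and not monotone.
- A separate simulation gave reductions of about 5%, 11% and 15% at C of about 0.63, 0.71 and 0.74.
- A third (300 trials per scenario) used log-odds per SD of 0.5, 0.9 and 1.3. The empirical SD of log RR went from 0.1170 to 0.1167, 0.1150 to 0.1109 and 0.1095 to 0.0997. Squaring the ratios gives variance reductions of about 1%, 7% and 17%. Power moved from 88 to 88%, 90 to 91% and 92 to 95%, with Monte Carlo error of about 2 points. With no true effect, variance fell by about 6%, 11% and 23%, and the unadjusted model rejected in 5 to 6% of trials.
- Both models aim at nearly the same value. At log-odds 0.9 the mean log RR was −0.364 unadjusted and −0.358 adjusted, against a true −0.357.
- The 40.1% is a yearly rate and the outcome is at six months. With an assumed six-month risk of 20.1% (half) to 22.6% (constant hazard, 1 − √0.599), the gains in estimated variance shrink to about 3%, 8 to 9% and 11% (250 trials per scenario).

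**4. Chance case mix.** With 400 patients per arm, the between-arm difference in a covariate of unit SD has standard error √[(2/400)(1 + 9ρ)], where ρ is the covariate's own ICC (assumed). For ρ = 0, 0.05 and 0.10 this is 0.071, 0.085 and 0.097, so 95% of trials fall within ±0.14, ±0.17 and ±0.19 SD.

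**5. Could case mix differ systematically?** The article does not settle this.

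- Section 2.7.1 randomises practices after recruitment, and Section 2.8 lists recruiters among those to be blinded.
- Section 2.7.2 discloses allocation to those who recruit. Section 2.7.3 sends the recruiter the allocation list and has patients placed from the monthly reports. Table 1 puts randomisation at T−1, alongside invitation and consent.
- Section 2.3.3 excludes patients whose diagnosis is ruled out after first contact with primary care or teleconsultation. Only the intervention arm has teleconsultation.

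**The case against.** The strongest reply is that nothing quoted is wrong. GEE by practice with adjustment for the randomisation strata is a standard analysis for this design, and the planned power is met without more. This stands in full.

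The article also never says that these are the sole covariates. It is a condensed report, and an analysis plan that is not shown may list others. This stands too: the point rests on what the article names, not on an exclusion of anything else.

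A reader might infer that the strata-only model carries patient-mix differences into the primary result as bias. The documents do not support that. Randomising 40 practices per arm balances patient factors in expectation, and the cluster-robust interval already allows for chance imbalance. A shift of 0.2 SD in one direction would by itself give a relative risk of about 0.95 (C 0.63) or 0.92 (C 0.70) with no true effect, but it lies just beyond the 95% chance range in step 4. A systematic shift would need recruitment or exclusion that differs by arm. The sections in step 5 make that possible, contradict one another, and do not show that it will happen. Adjustment would in any case correct only measured differences.

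The size is also open to challenge. The prognostic strength is assumed, and one known score flatters the gain compared with six coefficients estimated from partly missing records. Adjustment is not free either: under Section 3.1, intervention-arm physicians and cardiologists enter the same fields on the e-consultation form, so the baseline source must be fixed.

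**Conclusion.** The point holds as a cheap improvement to an acceptable model. The expected gain is a variance of log RR lower by roughly 5 to 15% if baseline covariates reach a C-statistic of about 0.63 to 0.74 at a 40.1% risk. It is less at a six-month risk near 20%, and close to nil for a weak score. In power, that is about 2 to 7 points at 80 clusters for R² of 5 to 20% by formula, and 0 to 3 points in the simulation.

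The documents support neither a finding that the primary analysis is invalid or underpowered for want of these covariates, nor one that its result will be biased by case mix. Protection against a measured systematic difference is a secondary benefit. It matters only if recruitment or post-allocation exclusion does differ by arm.

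**What to change.** Before unblinding, add to Section 2.11.2 that the primary GEE model includes, beside the two stratification factors, age, sex, length of index stay, NYHA class, systolic blood pressure and creatinine. Ejection fraction can stay off this short list, because it depends on an echocardiogram being on record and the article does not say how complete it will be.

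State three rules with it:

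- **Source.** In both arms, take values from the municipal report and the recruitment or health-record form dated at or before T0, never from the e-consultation form.
- **Missing values.** Fill missing covariates by single imputation that uses neither arm nor outcome.
- **Sensitivity.** Report the strata-only model beside the primary one.

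Separately, reconcile Sections 2.3.3, 2.7.1 to 2.7.3, 2.8 and Table 1 on when practices are randomised, who knows the allocation while recruiting, and whether exclusion after allocation can differ by arm. Covariate adjustment does not replace this.

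The cost is a few sentences, a little more code, and the rules for covariate source and missing values. No new data are needed.
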